### Comparison arm {6b}

The children in the comparison arm receive routine home visits by government health staff [61].

All participants (women and infants) in both arms are free to access their usual care pathways including free services provided through the government health system.

### Outcome measures {12}

The primary outcomes include attained weight, and weight for age *Z* scores at 12 months of age.

The secondary outcomes along with timing of their measurements are listed in Additional file 4. The key secondary outcomes for children are proportion stunted, wasted, and underweight at 6 and 12 months; overweight or obesity at 12 months; weight and length velocities between birth to 6 months and 6 to 12 months; neurodevelopment (composite cognitive, language, motor, socio-emotional, temperament and HOME scores; Mean Global Scale for Early Development score) at 12 months [62]; morbidity and hospitalization from birth to 12 months; and dietary assessment, micronutrients, and anemia status at 12 months (in a sub-sample).

The key secondary outcomes for mothers (Additional file 5) are depressive symptoms, nutritional status during the postpartum period, and household consumption and expenditures at 6 and 12 months of infant age, as well as dietary assessment at 3 and 6 months (in a sub-sample).

## Study procedures

### Surveillance, follow-up, screening, and enrollment

A pregnancy surveillance team (PST) conducts a door-to-door survey to list all pregnancies within 20 weeks of gestation based on the last menstrual period (LMP) or previous ultrasound and takes consent for ultrasound, regular contacts during pregnancy, and birth weight measurement within 72 h of childbirth. The team offers to facilitate the dating ultrasound in designated USG centers and transportation for the same. The details of pregnant women with gestational age < 20 weeks based on ultrasound are communicated to the pregnancy follow-up, screening, and enrolment team (PSE) (Fig. 1).

**Fig. 1 Fig1:**
[figure not shown]
Trial profile

During follow-up, pregnant women are counselled by field assistants (FAs) to register and deliver in a hospital, attend regular antenatal care clinics, consume an adequate diet, recognize danger signs in pregnancy, and initiate of breastfeeding early after birth. The field assistants periodically contact the identified women over the phone (through home visits if phone calls are unsuccessful), more frequently in the last trimester. For all live births, the team measures the baby’s weight within 72 h of birth and screens using inclusion and exclusion criteria. If the inclusion criteria are met, there are no exclusion criteria, and consent is given; the mother-infant pair is randomized to the intervention or control arm in the relevant stratum (preterm or term SGA). Post enrollment, baseline information is collected, including sociodemographic characteristics and recent childbirth related details including care received after delivery.

### Randomization, allocation concealment, and masking {16a, 16b, 16c, 17a}

The randomization list was prepared by an independent statistician using random permuted blocks of varying sizes, stratified by preterm and term SGA infants. The arm allocation is done using a web-based system at the time of enrolment. There are no additional criteria for discontinuation or modification of allocated intervention. Masking of the study teams is not possible because of the nature of the intervention. However, attempts are made to keep the independent outcome ascertainment team unaware of the arm allocation, to the extent possible.

### Intervention delivery

The PSE team informs the intervention delivery team about the infants randomized to the intervention arm. The intervention delivery teams conduct the first visit within 24 h of enrolment.

The intervention delivery visits are designed to accommodate the implementation of various components of intervention such as health, nutrition, and psychosocial in a single visit. On a particular visit, the focus is either on nutrition and health of the infant and mother or early child stimulation and responsive care and psychosocial care and support of the mother, with adjustments made as necessary. This intervention includes counselling on early and exclusive breastfeeding, expressing breast milk, kangaroo mother care, responsive feeding, micronutrient supplementation, hand washing, family planning, and immunization. The schedule includes 11 visits (days 1, 3, 7, 10, 11, 14, 17, 21, 22, 24, and 28) in the first 28 days, followed by visits every 2 weeks in months 2 and 3, and monthly visits in months 4, 5, and 6. In addition to providing counselling and support, the team also acknowledges and praises good practices.

During each visit, FAs ask about the well-being of both the infant and the mother. If the infant needs urgent care, the FA informs the supervisor and facilitates referral to the nearest health facility based on the family’s preference. The FA checks the mother’s understanding of the counselling messages and summarizes the key messages at the end of each visit.

If any problem with breastfeeding or complementary feeding is identified, a lactation counsellor or nutritionist intervenes to resolve the problem. If the problem is not resolved, the infants are referred to the pediatrician at the collaborating hospital.

The intervention delivery team FAs are measuring compliance with intervention during their home visits. This is done by both asking questions to the mother and observing empty food supplement packets or counting remaining tablets.

The pediatrician at the study clinic, located within the collaborating hospital, provides care for the infants in the intervention group and assesses infants with growth failure and associated illnesses. The lactation counsellor and nutritionist conduct home visits to assess breastfeeding and complementary feeding practices and counsel the mothers. Mothers of all infants with growth failure are assessed by a psychologist for any psychosocial problems that may pose hurdles in taking optimal care of the infant.

### Strategies to improve adherence to interventions {11c}

A system for electronic surveillance has been established to monitor infants who need extra care to ensure high adherence to intervention.

### Relevant concomitant care permitted or prohibited during the trial {11d}

Both groups of participants (intervention and control) have the freedom to utilize the standard care pathways, which include complimentary services from the government’s health system.

### Process evaluation and quality control

Two types of visits are conducted: observed visits and independent visits. Observed visits closely monitor worker activities, including family interactions, counselling quality, and procedure adherence. Coordinators perform monthly independent visits to ensure team adherence and accurate data collection. During pregnancy surveillance, activities involve observing rapport-building, survey-related messaging, assessing LMP, and consenting. During pregnancy follow-up, coordinators monitor the process of delivering counselling messages over the phone and handling inquiries from the participants. For screening and enrollment, criteria assessment, consenting, and anthropometric measurements are observed. Observation of outcome ascertainment focuses on the adequacy of anthropometric assessment methods. During intervention delivery, supervisors observe feeding sessions, breastfeeding practices, and child stimulation activities for the first 6 months, and complementary feeding practices from 7 to 12 months, with all details related to compliance documented at each visit.

Supplements are provided every 2 weeks, and at the time of delivery, the team asks questions on supplement consumption since the last visit and counts the remaining tablets to monitor compliance.

### Outcome ascertainment {18a}

Infants in both the intervention and control arms are visited at home by an independent outcome ascertainment team in pairs, at infant ages 1, 3, 6, 9, and 12 months, to measure weight, length, and head and mid upper arm circumference (MUAC); assess infant care practices; and document the prevalence of reported illnesses in the previous 2 weeks and care-seeking for illness and hospitalizations since the last visit. Additionally, the team measures the weight and MUAC of mothers at 2, 6, and 12 months postpartum and assesses postpartum depression among mothers using the Edinburgh Postnatal Depression Scale (EPDS), which has been validated for use in India [63].

Weight measurements are obtained using digital weighing scales (Seca model 354; California, USA) with an accuracy of up to 10 g, while infant length measurements are taken using infantometers (Seca model 417; California, USA) with a precision of 0.1 centimeters. Head and MUAC are taken using a measuring tape (model 212; Seca, California, USA) [64–66].

Information on household consumption and expenditures (monthly expenses on food, rent, health care, utilities, maintenance, fuel, reimbursement of loans, and helpers; education and health care expenses in the preceding three months; annual expenses on insurance, and clothes) will be collected at enrollment and 6 and 12 months of age. Neurodevelopmental assessment is done by trained and standardized psychologists. Cognitive, motor, language, and socio-emotional development will be assessed at 12 months of age using the Bayley Scales of Infant and Toddler Development III (BSID-III) [67]. Infant temperament will be assessed at 12 months of age using the Infant Temperament Scale [67, 68]. The child’s home environment will be assessed using the Home Observation of the Environment (HOME) questionnaire (Infant and Toddler version [69]) by the trained field team through physical home visits. Additionally, the Global Scales for Early Development (GSED) scale will be used at 6 and 12 months to assess child development across multiple domains, including cognitive, motor, and social-emotional development. Blood samples (~10 ml) will be collected at 12 months of age for micronutrient assays. The samples will be centrifuged, and serum and blood pellet stored at – 80 °C in the field office. The micronutrient concentrations will be measured in accredited laboratories.

Dietary assessment is done using: a food frequency questionnaire (FFQ) and 24-h dietary recall (subsample) at 9-month and 12-month outcome visits. Mothers of infants will be asked to provide information regarding their child’s food consumption in the previous 24-h duration. The collected data from these recalls will be entered into the DietCal software [70].

Ultrasounds for assessment of preterm birth are done at designated ultrasound centers. A trans-abdominal USG is scheduled between 9 and 13 weeks of gestation to estimate gestational age calculated by fetal crown length. If CRL is > 95 mm, femur length and head circumference are used to assess gestational age. All digital images are taken by trained radiologists according to intergrowth standards. Ten percent of all USG scans are randomly selected and sent to external reviewer for quality assurance.

Participants who discontinue the intervention will be treated as censored data and will be included in the analysis up to the point of discontinuation.

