### Main effects

The primary outcome will be analyzed using an intention-to-treat (ITT) approach. All participants randomized to a treatment group will be included in the analysis, regardless of their adherence to interventions. However, missing data on the primary outcome at 12 months will not be imputed since the key assumption that data will be missing at random would probably not be valid. However, we will use imputation methods depending on the nature of missingness for the secondary outcomes. Some authors might call the above approach modified intention-to-treat analysis; however, there is no clear consensus on the use of this terminology as per the CONSORT guidelines. The statistical precision of the effects will be presented as 95% confidence intervals (Cis). The distributions of WAZ will be presented in Epanechnikov kernel density plots by study arms. To quantify any differences in distribution, the 5th, 10th, 15th, 20th, and… up to the 95th percentiles will be compared using quantile regression. The 95% CI of the difference between the percentile estimates for the two arms will be calculated using bootstrap resampling with 1000 replacements. The percentile differences and corresponding CIs will be visualized in forest plots.

For binary outcomes, we will use generalized linear models (GLMs) of the binomial family with a log-link and an identity-link function to calculate the relative risks and risk differences, respectively. For continuous outcomes, GLMs of the Gaussian family with an identity-link function will be used to calculate the difference in means between the groups.

The effect of the intervention package on infant mortality across both strata will be estimated in a Cox proportional hazards model taking the stratification variable into account. The days of follow-up for each infant will be calculated as the date of enrolment subtracted from the date of the last follow-up or death.

We will adjust for imbalances in baseline features if present.

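### Censoring infants when they stop the intervention contradicts the intention-to-treat rule and can remove measured infants from one arm of the primary comparison

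*Protocol article*

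**What the plan says.** The last sentence of Outcome ascertainment {18a} reads: "Participants who discontinue the intervention will be treated as censored data and will be included in the analysis up to the point of discontinuation". It names no outcome, no model and no limit on its scope.

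Main effects gives a different rule. "The primary outcome will be analyzed using an intention-to-treat (ITT) approach", and then: "All participants randomized to a treatment group will be included in the analysis, regardless of their adherence to interventions". It adds that "missing data on the primary outcome at 12 months will not be imputed". For mortality, days of follow-up in the Cox model are "calculated as the date of enrolment subtracted from the date of the last follow-up or death", so they do not end at discontinuation.

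Three further statements decide what the conflict means in practice:

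- Outcome measures {12}: "The primary outcomes include attained weight, and weight for age *Z* scores at 12 months of age".
- Outcome ascertainment {18a}: "Infants in both the intervention and control arms are visited at home by an independent outcome ascertainment team in pairs". The visits are at 1, 3, 6, 9 and 12 months.
- Comparison arm {6b}: "The children in the comparison arm receive routine home visits by government health staff". Controls get routine care and no part of the trial package.

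**The concern.** Stopping the intervention is the extreme form of non-adherence. Main effects keeps such an infant in the analysis. The sentence in Outcome ascertainment discards everything measured after the stop. Two analysts could each follow the protocol and analyse different sets of infants for the primary outcome.

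For a single 12-month measurement, data kept up to an earlier stopping date means no primary outcome. Take a family that stops in month 7 whose child is weighed by the outcome team at month 12. Under one rule the child counts. Under the other the weight is set aside and, without imputation, the child leaves the comparison. Main effects itself doubts that missing 12-month data are missing at random, so the censoring rule would add missingness of a kind the authors already distrust.

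Controls have no trial package to discontinue, so the exclusion falls on the intervention arm. The document does not say this outright; it follows from the design. At stake is whether the primary result in each stratum still compares the groups as randomised. The sentence would also reach other 12-month outcomes, such as the Bayley scores.

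**Working it through.** **1. The rules side by side**

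| Question | Outcome ascertainment {18a} | Main effects |
|---|---|---|
| Infant stops the package, weighed at 12 months | 12-month weight not used | 12-month weight used |
| Infant stops the package, later dies | Time ends at the stop | Time runs to death |
| Infant leaves the study altogether | No 12-month weight | No 12-month weight, not imputed |

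The rules differ in the first two rows only. For the primary outcome, what matters is the number of infants who stop the package and are still measured at 12 months.

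**2. The plan's own sample size**

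Inputs from Sample size {14} and Recruitment {15}: difference 0.20 SD, 90% power, 95% confidence (taken as two-sided 5%), 20% loss, 650 enrolled per arm per stratum.

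- n per arm = 2(1.960 + 1.282)² / 0.20² = 526 by the normal formula. The t-based solution is 526.3, rounded up to the stated 527.
- 527 / (1 − 0.20) = 659, against 650 stated, a difference under 3%.
- Infants measured at 12 months: 650 × 0.80 = 520 per arm, which gives power 0.897.

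**3. Effect of applying the censoring rule**

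Two quantities are assumptions, because the document gives neither:

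- d = share of the 520 measurable intervention infants who stopped the package.
- g = how far those infants lie below continuers, in SD units.

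The mean of the whole intervention arm is (continuers' mean − d × g). Removing those who stopped leaves the continuers' mean, so:

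- bias = d × g
- SE = √[1/(520(1 − d)) + 1/520]
- type I error = Φ(−1.96 + bias/SE) + Φ(−1.96 − bias/SE)

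Example with d = 0.10 and g = 0.5: bias = 0.05; SE = √(1/468 + 1/520) = 0.0637; bias/SE = 0.785; type I error = Φ(−1.175) + Φ(−2.745) = 0.123.

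| d | Intervention infants left | Power at 0.20 SD, no bias | g = 0.3: bias, type I error | g = 0.5: bias, type I error |
|---|---|---|---|---|
| 5% | 494 | 0.889 | 0.015 SD, 5.7% | 0.025 SD, 6.8% |
| 10% | 468 | 0.881 | 0.03 SD, 7.6% | 0.05 SD, 12.3% |
| 20% | 416 | 0.860 | 0.06 SD, 14.9% | 0.10 SD, 33.0% |

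The protocol equates 0.20 SD with 200 g, so 0.015 to 0.10 SD is 15 to 100 g. If those who stop do better than continuers, g changes sign: the bias has the same size against the package, and the two-sided error rate is unchanged. The loss of power is small. The harm is bias.

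**The case against.** The strongest defence is that Main effects is the specific rule for the primary outcome and the other sentence is stray. It closes a data-collection section, after dietary recall and ultrasound procedures, and speaks of censoring, a time-to-event term that does not fit one 12-month weight. The authors may have meant families who withdraw, with data kept up to withdrawal. That may be the intention, but the text speaks of discontinuing the intervention and sets no limit to time-to-event outcomes. Restricting it to mortality does not help either, because the Cox follow-up definition runs to last follow-up or death. This is also not a detail left to an analysis plan: two stated rules conflict.

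Other parts of the defence stand, and they rule out four stronger conclusions that a reader might draw:

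- *The primary comparison becomes adherers against all controls.* The sentence covers those who discontinue. Poor compliers who never stop remain under both rules.
- *The mortality analysis will be informatively censored.* The Main effects definition of follow-up time says otherwise. What exists is a second conflict with the censoring sentence, not a settled plan.
- *The bias favours the package.* Nothing in the document says who stops. Families of ailing infants might, and so might families of thriving ones.
- *The error rate will be 33%.* That case needs 20% of the infants still measured at 12 months to have stopped, on top of the 20% loss already allowed for. Those who stop and those who leave may overlap heavily, and leavers are missing under either rule.

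**Conclusion.** The contradiction is certain on the text and must be resolved, because it decides who enters the primary analysis in both strata. Applied as written, the censoring sentence would exclude infants who stopped the package but were measured at 12 months, in effect from the intervention arm only, and the comparison would no longer be by intention to treat.

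The size is conditional. With d from 5% to 20% of measurable intervention infants and g from 0.3 to 0.5 SD, both assumed, the bias runs from 0.015 SD, which is negligible, to 0.10 SD, half the target effect. Type I error runs from about 6% to 33%. These figures further assume 520 measured infants per arm, equal variances and a normal approximation. Few discontinuers, or discontinuers who resemble continuers, would make the harm small. The direction cannot be stated from the document.

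**What to change.** Delete the censoring sentence from Outcome ascertainment {18a} and state instead that:

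1. outcome visits continue after a family stops the intervention;
2. all measurements obtained are analysed by randomised arm, whatever the adherence;
3. an infant's data end only at loss to follow-up, withdrawal of consent for data collection, death or end of follow-up, in line with the follow-up definition under Main effects.

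If withdrawal from follow-up was what the sentence meant, it should say so in those terms. An adherence-based analysis can be added if it is labelled supplementary.

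The change is a few lines in the protocol and analysis plan. It alters no sample size, and the 12-month visit is already scheduled in both arms. One cost may not be avoidable. The document does not say that visits continued after discontinuation, and recruitment began on 24 January 2023. Any measurement not taken before the correction cannot be recovered and should be reported as missing, by arm.

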### Training and standardization

Staff are trained in the overall study objectives, strategies, and in their job responsibilities. Additionally, each team receives intensive training in their area of work along with training in Good Clinical Practice (GCP) guidelines.

Inter- and intra-observer standardization exercises for weight, length measurements, head circumference, and MUAC were conducted at the beginning of the study and will be repeated every 6 months. Weighing scales and infantometers are calibrated daily using standard weights and length measurement rods [56].

The psychologists undergo inter- and intra-observer standardization exercises for Bayley assessments. In addition, 10% assessments will be done by 2 psychologists. Agreement between the measurements assessed by the intra-cluster correlation coefficient (ICC) and by calculating Lin’s concordance correlation coefficient [71].

### Study oversight

Coordinators designated for each activity oversee the work of their teams. Weekly status reports are shared with the investigators. Periodic review meetings are held between the study teams, coordinators, and investigators.

The Centre for Intervention Science in Maternal and Child Health (CISMAC) is responsible for the oversight of the study. Technical staff from CISMAC interact with the investigators through monthly conference calls and twice-yearly site visits to review the study progress.

### Data management {#19}

A data management center is set up in the field office where real-time data is transferred to the server. Data is captured electronically on tablets and mobile phones and uploaded to an access-controlled cloud server. Range and logical checks have been incorporated to reduce errors. Additional logical and across-form checks are run twice weekly. Queries generated are given to study teams, and necessary corrections to the database are logged.

### Data safety monitoring committee (DSMC) {21a, 21b}

CISMAC has established a DSMC to oversee the study’s progress and evaluate the safety of the intervention. The members include an epidemiologist, a statistician, a pediatrician, and a social scientist. The committee reviews data on adverse events to supplements and deaths quarterly and meets twice a year. The committee suggested that trial-stopping rules will be dependent on the number of interim analyses that may be planned. For efficacy, interim analysis each of the two strata O’Brien Fleming’s rule will be followed. This rule is a group sequential method that sets increasingly stringent boundaries for statistical significance as the data accrue, thus controlling the overall type I error rate. For safety interim analysis in each of the two strata, Pocock’s rule will be followed. This rule uses a constant boundary for statistical significance, allowing for regular monitoring of the data without inflating the type I error rate. The first interim analysis will be conducted when 50% of enrolments have occurred in both strata. These stopping rules will ensure that the trial can be stopped early if there is clear evidence of benefit or harm, while also maintaining the integrity of the study results. The approach taken to these analyses will be rigorous and will adhere to the highest standards of statistical practice.

